#### Study setting

Patient enrolment for the ITREMA trial was done between June 2015 and August 2017 at the Ndlovu Medical Centre in Elandsdoorn, Limpopo Province, South Africa.

#### Sampling/Sample size

All the records from ITREMA database will be used. There are 501 ART patients in the ITREMA database.

#### Data collection

Data will be extracted from the ITREMA databases. The ITREMA database contains fields for socio-demographics and psychosocial characteristics. The control variables include sex, age, level of education, employment status, sources of income, household members, food security, mental health, HIV self-efficacy and HIV related stigma (see S1 Appendix study codebook and S6 Appendix ITREMA questionnaire). The data will be exported to STATA 15.1 for data cleaning and analysis.

*Outcome*. Self-reported non-adherence will be measured using three items from the ACTG questionnaire [52]: “How often do you have difficulty in taking your medication on time?, with responses given on 4-point scale (All the time, Most of the time, Rarely, Never), “On average how many days per week would you say that you missed at least one dose of your medication?”, with responses given on a 6-point scale (every day, 4–6 days per week, 2–3 days per week, Once a week, Less than once a week, Never), and “When was the last time you missed taking any of your medications?”, with responses also given on a 6-point scale (Past week, 1–2 weeks ago, 2–4 weeks ago, 1–3 months ago, More than 3 months ago, Never) (see S6 Appendix ITREMA questionnaire). Responding ‘never’ to all three questions will be taken to indicate good self-reported adherence. Suboptimal adherence measured using pill count is defined as a pill count <95%. This threshold is aligned with the WHO cut-off, which considers a pill count ≥ 95% as good adherence for patients taking ART [53]. Virological failure will be defined as viremia ≥1000 copies/ml within 96 weeks of follow-up [48,49].

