#### Data analysis

Data will be coded and analysed using STATA version 15.1. Tests of association (Chi-square and t-test) between outcome variables and selected demographics characteristics and clinic indicators will be conducted. Outcome variables will include viral load detectability and retention outcomes (active in care, transferred-out, lost to follow-up and dead),. Regression analysis, univariate and multivariate analyses between variables will be built for outcome variables to identify independent predictors. Variables such as age, sex, health facility, baseline regimen, ART start date, baseline CD4 count, most recent CD4 count, ART visit dates, and months on ART will be considered as predictor variables or independent variables. Analysis will include survival analysis which will consider different entry time points into the ART program. Subsequently, patients will not be grouped all together but will be followed up in a 12-month interval when measuring the outcomes (virological failure and lost to follow up).

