#### Study design

This cohort study using secondary data analysis will be conducted as a sub-study of the Intensified Treatment Monitoring Accumulation (ITREMA) study (Clinicaltrials.gov Identifier NCT03357588) [51]. The ITREMA database will be used to extract ART information. ITREMA is an open-label randomised clinical trial evaluating different treatment monitoring strategies for first-line ART, which ran from June 2015 to January 2019 [51]. ITREMA was conducted at the Ndlovu medical centre in Limpopo province, South Africa. The ITREMA study enrolled adult PLHIV and assessed an intensified HIV-treatment monitoring strategy in a randomised comparison with a control group receiving standard-of-care HIV treatment in accordance with the South Africa National Department of Health guidelines

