#### Data analysis

Data will be coded and analysed using STATA version 15.1. Tests of association (Chi-square and t-test) between outcome variables and selected socio-demographics and health related characteristics will be conducted. Outcome variables will include (but not limited to) viral load detectability, retention outcomes (active in care, transferred-out, lost to follow-up and dead), side effects and treatment interruptions (stop and restarting treatment). Regression analysis, univariate and multivariate analyses between variables will be built for outcome variables to identify independent predictors. Variables such as age, sex, health facility, beliefs, education, economic status, employment status, religious status, disclosure, and months on ART will be considered as predictor variables or independent variables.

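### Phase II uses a 96-week virological failure outcome that late ITREMA enrolees cannot complete, and gives no rule or time-to-event method for incomplete follow-up

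*Protocol article*

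**What the plan says.** All references are to the protocol article, Materials and methods.

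- Phase II, Data collection (Outcome): "Virological failure will be defined as viremia ≥1000 copies/ml within 96 weeks of follow-up".
- Phase II, Sampling/Sample size: every record is used. "There are 501 ART patients in the ITREMA database".
- Phase II, Study setting: "Patient enrolment for the ITREMA trial was done between June 2015 and August 2017". Phase II, Study design, says of the trial: "which ran from June 2015 to January 2019".
- Phase II, Data analysis: "Tests of association (Chi-square and t-test) between outcome variables and selected socio-demographics and health related characteristics will be conducted", followed by "Regression analysis, univariate and multivariate analyses between variables will be built for outcome variables to identify independent predictors". No type of regression is named. The outcomes listed there include "retention outcomes (active in care, transferred-out, lost to follow-up and dead), side effects and treatment interruptions".
- Phase I, Data analysis, by contrast: "Analysis will include survival analysis which will consider different entry time points into the ART program". Phase I also excludes records with missing data and sets its inclusion cut-off so that everyone has at least 12 months of follow-up. Phase II has no counterpart to any of these.

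**The concern.** A fixed 96-week window gives everyone the same chance of being seen to fail only if everyone is observed for 96 weeks or until failure. Phase II has staggered entry and a single closing month, and it lists loss to follow-up, transfer and death among its outcomes, so some people will have neither a failure nor a full window. A chi-square test on failure within 96 weeks needs each person placed in a failed or not-failed cell, or left out. The text does not say which.

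Phase II exists to find factors associated with failure. A factor that affects only how long people stay under observation can then appear associated with failure, and the direction of that artefact depends on the unstated rule.

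**Working it through.** The document gives no sample-size, power or event figure for Phase II and no share with incomplete follow-up, so there is no stated figure to reproduce. The check is date arithmetic followed by an illustration.

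**Step 1. Last enrolment date that allows 96 weeks.** Trial end minus 96 × 7 = 672 days, taking follow-up to close in January 2019 and the window to run from ITREMA enrolment.
- Close on 1 January 2019: 28 February 2017.
- Close on 31 January 2019: 30 March 2017.

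The last possible enrolee has about 70 weeks (31 August 2017 to 1 January 2019, 69.7) to 78 weeks (1 August 2017 to 31 January 2019, 78.3).

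**Step 2. Share of the cohort affected.** Share = (end of enrolment − last full-window date) / length of enrolment. This needs an accrual pattern, which the document does not give.
- Uniform accrual, 1 June 2015 to 31 August 2017 (822 days): 154/822 = 18.7% (94 of 501) to 184/822 = 22.4% (112 of 501).
- Uniform accrual, varying the unstated days within the stated months: 15.7% to 23.2% (78 to 116 of 501).
- Accrual falling linearly to zero, with u the fraction of the enrolment period before the cut-off (0.776 or 0.813): (1 − u)² = 5.0% or 3.5%.
- Accrual rising linearly from zero: 1 − u² = 39.8% or 34.0%.

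**Step 3. Effect of the unstated rule.** Assumptions, for illustration only: uniform accrual, constant failure hazard h, constant non-informative dropout hazard g, true 96-week risk 20%. Then h = −ln(0.80)/96 = 0.00232 per week. With 20% dropout by week 96, g has the same value. For a person with possible follow-up F weeks (at most 96), the chance of an observed failure is h/(h+g) × [1 − exp(−(h+g)F)]. Averaging over enrolment dates gives A. The fraction observed for 96 weeks without failure is B = u × 0.80 × (1 − dropout).

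Unresolved people scored as non-failures give A. Excluding them gives A/(A+B).

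| Trial close | Dropout | A (scored as non-failure) | B | A/(A+B) (excluded) |
|---|---|---|---|---|
| 1 Jan 2019 | 0% | 19.4% | 62.1% | 23.8% |
| 31 Jan 2019 | 0% | 19.6% | 65.0% | 23.2% |
| 1 Jan 2019 | 20% | 17.5% | 49.7% | 26.1% |
| 31 Jan 2019 | 20% | 17.7% | 52.0% | 25.4% |

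For a true 30% with 20% dropout the same formulas give 26.4% to 26.6% (scored as non-failure) and 36.9% to 37.8% (excluded). The two rules therefore differ by about 8 to 11 percentage points.

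**Step 4. Effect on an association.** Take two groups with the same true risk of 20%, one with 10% dropout and the other with 30%.
- Scored as non-failures: 18.5% to 18.7% against 16.5% to 16.7%, a risk ratio of about 0.89.
- Excluded: 24.2% to 24.9% against 26.8% to 27.6%, a risk ratio of about 1.11.

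The true ratio is 1. The artefact is modest, and it changes direction with the rule.

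**The case against.** The strongest reply is that this is a condensed article. The type of regression, the censoring and the handling of short follow-up may sit in a fuller plan, and a Cox model is compatible with the wording. Loss to follow-up, transfer and death are at least recorded as outcomes. The 96 weeks can be read as an upper limit that nobody is required to reach, and the latest enrolees still have about 70 weeks or more.

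Part of this stands. The loss from late enrolment alone is small: mean possible follow-up is about 93 to 94 weeks, and the risk falls by 0.4 to 0.6 points at an assumed 20% if these people are scored as non-failures. The dropout rate and the true risk above are assumptions. The 20% to 30% in the Introduction mixes clinical, immunological and virological failure nationally, so it is not a 96-week ITREMA figure.

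What does not stand is that this is only detail left out. The article does give this detail for Phase I, where entry is also staggered. For Phase II it fixes a window that its own dates do not allow for all records, and names only tests that treat the outcome as complete.

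Several stronger readings are tempting, but the text does not support them:
- That the plan scores dropouts as non-failures. It states no rule; exclusion and censoring fit the wording equally well.
- That the dates alone show a fifth of the cohort to be short. They give a cut-off date; the share needs an accrual pattern.
- That enrolment date becomes an artefactual predictor. It is not among the predictors named for Phase II.
- That a viral load taken at enrolment counts as failure. The definition refers to follow-up, and the article does not say whether people starting ART were enrolled.

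**Conclusion.** The point holds in limited form. If follow-up closed with the trial in January 2019 and the window runs from enrolment, people enrolled after about 28 February to 30 March 2017 cannot complete it. They make up about 16% to 23% of 501 under uniform accrual, and about 4% to 40% under the other patterns tried. Phase II names no method suited to unequal follow-up and no rule for people without a complete window.

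Scoring those people as non-failures understates the risk, slightly from late enrolment and more once dropout is added. Dropping those who neither failed nor completed overstates it, because late enrolees and leavers then enter only if they fail. Restricting to early enrolees by date, whether or not they failed, would remove the late-enrolment error but not the dropout error.

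The date conflict and the missing rule are certain on those two conditions. The size of the bias is illustrative, and its direction depends on a choice the document does not make. The change is worth making but is not critical to the study.

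**What to change.** In Phase II, Data analysis, define the outcome as time from ITREMA enrolment to first viral load of 1000 copies/ml or more. Analyse it with Kaplan-Meier curves and Cox regression, or interval-censored regression since viral load is known only at sampling dates. Censor at the earliest of the last viral load, database close and 96 weeks, and say how death and transfer are treated. Report how many people had a viral load around week 96, and how many were short because of late enrolment and because of leaving.

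If a yes/no outcome is kept as well, state the rule for people without a complete window and show the result under both scoring and exclusion.

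This brings Phase II into line with the survival analysis planned for Phase I. The cost is a few sentences and a little more analysis work, provided the ITREMA extract holds enrolment and viral-load dates, which the article does not list explicitly. Censoring assumes that leaving is unrelated to failure given the covariates. If leavers are likelier to fail, some bias remains and a sensitivity analysis would be needed.

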#### Data analysis

Data will be coded and analysed using STATA version 15.1. Tests of association (Chi-square and t-test) between outcome variables and selected socio-demographics and health related characteristics will be conducted. Outcome variables will include (but not limited to) viral load detectability, retention outcomes (active in care, transferred-out, lost to follow-up and dead), side effects and treatment interruptions (stop and restarting treatment). Regression analysis, univariate and multivariate analyses between variables will be built for outcome variables to identify independent predictors. Variables such as age, sex, health facility, beliefs, education, economic status, employment status, religious status, disclosure, and months on ART will be considered as predictor variables or independent variables.

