#### Strengths and limitations

To our knowledge this will be the first study using a social-ecological perspective and a convergent parallel mixed method design to report on combination ART in South Africa. Combining quantitative and qualitative data from public health settings, a controlled environment, the patient perspective and evidence from the region will enable us to make recommendations for a comprehensive, acceptable, and appropriate adherence strategy for the country.

The study presents a fewlimitations. The study will be conducted in a total of eight health facilities (seven of over 120 health facilities in one South African metropolitan municipality (urban setting) and one facility in a rural setting). Therefore, findings may not be generalizable to other municipalities and districts in South Africa, or to other country settings. Furthermore, although there are efforts to ensure good quality of data by the South African Department of Health, supporting partners and research staff, secondary data are subject to quality issues, due to data inconsistencies and missing data. Other potential predictors of adherence, such as disclosure, stigma, and self-reported adherence, will be assessed through a standard questionnaire. This may lead to reporting bias (memory and social desirability biases). Policy-level factors might not probe for relevant factors due to how this study is designed (with it focus on the individual’s awareness of health policies and guidelines which is insufficient to fully assess policy-level factors).

In conclusion, our study will demonstrate how an existing socio-ecological conceptual framework can be used as a tool to provide guidance regarding facilitators and barriers to ART adherence. By populating this framework through secondary data analysis, participant interviews of PLHIV who are taking ART and a systematic review comparing adherence intervention strategies for the chronic conditions, this mixed method study will provide evidence on factors affecting treatment adherence at different socio-ecological levels and guide context-specific intervention strategies to improve ART adherence. We believe that the use of our study results to strengthen adherence intervention will subsequently improve health outcomes and decrease the number of patients switching to complex treatment such as second-line and third-line regimens.

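### Phase II pools both randomised ITREMA monitoring arms without naming arm as a covariate, lists a facility term that is constant, and defines virological failure in a way that can depend on how often viral load was tested

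*Protocol article*

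**What the plan says.** The Phase II Study design section describes ITREMA as an open-label randomised trial that "assessed an intensified HIV-treatment monitoring strategy in a randomised comparison with a control group receiving standard-of-care HIV treatment". It names one site: "ITREMA was conducted at the Ndlovu medical centre in Limpopo province, South Africa". Strengths and limitations confirms this, counting "one facility in a rural setting".

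Under Sampling/Sample size, "All the records from ITREMA database will be used", and "There are 501 ART patients in the ITREMA database". Both arms are therefore analysed together.

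The Phase II Data collection section gives a control list of socio-demographic and psychosocial variables, among them "food security, mental health, HIV self-efficacy and HIV related stigma". It defines virological failure as viraemia of 1000 copies/ml or more within 96 weeks of follow-up. It does not say at which visit, or from how many tests.

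The Phase II Data analysis section plans regression models to identify independent predictors. Its candidates are "Variables such as age, sex, health facility, beliefs, education, economic status, employment status, religious status, disclosure, and months on ART". Randomised arm is in neither list, and no Phase II section mentions stratifying or restricting by arm.

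**The concern.** The source trial has one design variable, the monitoring strategy, and the analysis lists do not mention it. They do name a facility variable that takes a single value in this data set.

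Two things are at stake:

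- **The outcome.** A threshold crossing at an unspecified time within a window is more likely to be seen the more often one looks. If the arms had different viral load schedules, failure status would mix true viraemia with testing frequency.
- **The predictor estimates.** Omitting a factor related to the outcome pulls odds ratios for balanced predictors towards 1. For a predictor that the monitoring strategy can itself change, omitting arm can create a spurious association. The article does not say at which visit the psychosocial variables are taken, so the second case cannot be ruled out.

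**Working it through.** Phase II states no power or sample-size figure (501 is a database count), so there is none to reproduce.

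**1. Text check.** Data collection (controls) and Data analysis (predictors) do not name arm. Sampling takes every record. Study design states two randomised strategies at one centre.

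**2. Facility term.** With 501 patients at one site, the facility column is a constant. Intercept plus facility gives a design matrix of rank 1, not 2, so the facility coefficient is not estimable. The same term appears in the Phase I list, where seven facilities make it vary.

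**3. Detected failure by number of tests.** The article gives neither tests per arm nor a per-test rate, so all inputs here are assumptions. Failure is read as at least one value at or above the threshold. With per-test probability p, k tests and independent tests:

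P(failure) = 1 − (1 − p)^k

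| Tests (standard v intensified) | p = 3% | p = 5% | p = 10% |
|---|---|---|---|
| 2 v 4 | 5.9% v 11.5%, OR 2.06 | 9.8% v 18.5%, OR 2.11 | 19.0% v 34.4%, OR 2.23 |
| 3 v 8 | 8.7% v 21.6%, OR 2.88 | 14.3% v 33.7%, OR 3.05 | 27.1% v 57.0%, OR 3.56 |
| 2 v 8 | 5.9% v 21.6%, OR 4.39 | 9.8% v 33.7%, OR 4.70 | 19.0% v 57.0%, OR 5.64 |

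Independence overstates the gap, because viral loads in one person are correlated. With a beta-binomial model, within-person correlation ρ and s = (1 − ρ)/ρ:

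P(failure) = 1 − ∏ [(1 − p)s + i] / [s + i], for i = 0 to k − 1

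- p = 5%, 2 v 8 tests, ρ = 0.3: 8.3% v 17.9%; OR = (0.179/0.821)/(0.083/0.917) = 2.41.
- p = 5%, 2 v 8 tests, ρ = 0.5: 7.4% v 12.9%; OR about 1.9.
- p = 3%, 2 v 4 tests, ρ = 0.5 (so s = 1): no failure is 0.97 × 1.97/2 = 0.955 with 2 tests, and 0.955 × 2.97/3 × 3.97/4 = 0.939 with 4. Failure is 4.5% v 6.1%; OR about 1.4.

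Over these assumptions the arm odds ratio from testing alone runs from about 1.4 to 5.6. With equal schedules it is 1.

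**4. Effect on predictor odds ratios.** This is the quantity Phase II reports. Assume 2 v 8 tests, p = 5%, independent tests, near-equal arms and a binary predictor with 40% prevalence.

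*Balanced baseline predictor, true OR 2.0.* Doubling the odds within each arm moves failure from 9.75% to 17.8% (standard) and from 33.7% to 50.4% (intensified). Averaged over arms this is 21.7% v 34.1%. The marginal OR is (0.341/0.659)/(0.217/0.783) = 1.86. A simulation (N = 501, 300 runs) gave 1.85 without arm and 2.00 with arm. A balanced null predictor stayed at 1.00.

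*Null predictor whose prevalence differs by arm.* With 35% v 45% prevalence, failure is (0.35 × 9.75 + 0.45 × 33.7)/0.80 = 23.2% among those with the factor and (0.65 × 9.75 + 0.55 × 33.7)/1.20 = 20.7% among those without. The OR is about 1.16 (simulation 1.15). A 20-point difference gave 1.35 in simulation. Adding arm returned both to about 1.00.

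With ρ = 0.3 the same steps, using 8.3% v 17.9%, give 1.96 in place of 1.86. The distortion shrinks as correlation rises.

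**The case against.** The strongest reply is that the article does not exclude arm. Both lists are introduced as examples, and the codebook and questionnaire in the appendices are not shown. That stands: a reader might infer that arm has been deliberately left out, and the text does not support so firm a statement. What can be said is that the article chose to name variables and named an inestimable one while not naming the trial's own allocation variable.

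The second reply is that randomisation protects baseline predictors such as age, sex and education. That also stands. A reader might take the large arm contrast in step 3 as the bias in the predictor estimates. It is not: for baseline predictors the effect is modest attenuation. Nor is every predictor measured after randomisation confounded by arm; that requires arm to affect the predictor as well as the outcome. The article reports no arm effect, so arm cannot be called a known strong factor.

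Third, the schedules are unknown and the simple formula assumes independent tests. This is why only a range is given.

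A reader might also infer that the Data analysis section has replaced the Phase II outcomes, since its list ("Outcome variables will include (but not limited to) viral load detectability, retention outcomes" and so on) does not mention self-reported adherence or pill count. The list is expressly non-exhaustive, and the objective, research question 2 and the Outcome paragraph all name the three outcomes. Likewise, calling stigma or food security controls does not remove them from study: in one regression, controls and predictors are fitted identically.

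Finally, a constant facility column drops out of the model and biases nothing. That is correct; it is an error in the list, not a source of bias.

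**Conclusion.** The point holds in a limited form. As written, the Phase II plan pools two randomised monitoring strategies without naming arm, names a facility term that cannot be estimated, and uses a failure definition that depends on testing frequency if schedules differ by arm.

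The textual part rests on no assumption. The size does: an arm odds ratio of about 1.4 to 5.6 from testing alone needs 2-3 versus 4-8 tests, 3-10% per test and within-person correlation between 0 and 0.5, none of which the article gives. For baseline predictors the consequence is modest, about 2.0 falling to 1.85 in the assumed 2 versus 8 scenario with independent tests, and less with correlated tests. For predictors that arm can shift, a spurious odds ratio of about 1.15 to 1.35 is possible in that scenario when prevalence differs by 10 to 20 points. The change is worth making because it is nearly free, not because the analysis would otherwise be invalid.

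**What to change.** - Include randomised arm as a covariate in every Phase II model, or stratify by it.
- Delete health facility from the Phase II predictor list.
- State the viral load schedule of each arm. If the schedules differ, derive virological failure from time points common to both arms in the primary version, and report the all-tests version as a sensitivity analysis.
- Give any statement of size as a range, with the assumed tests per arm, per-test rate and within-person correlation.

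Cost: the data are already collected. Arm is the trial's allocation variable and should be obtainable, although the article does not list it among the database fields. Adjustment uses one degree of freedom. Restricting to common time points removes some intensified-arm tests from the primary version and may lower the number of detected failures.
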